**Figure 1 F1:**
[figure not shown]
Outcome variables and time points of assessment.

### Sample size calculation

To estimate the sample size requirements, the target sample size was defined by a power analysis using the primary outcome, physical activity. The calculation was made using the accelerometer counts, and the activity level baseline mean and standard deviation for both groups was set based on the study of Winter et al. [22]. Based on these calculations, a total of 34 participants (17 to each group) would be needed to provide 80% power with a 5% significance level. As the survival rate is over 80%, we increased the target enrollment by 20%, resulting in a sample size of 40 patients. The treatment effect was set to 20% difference between groups targeting 360 gait cycles per day mean difference (assuming SD of 360 for the mean change) in the change between groups.

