### Data analysis

The quantitative data from the activity and fatigue questionnaires, M-ABC scores, accelerometers and metabolic risk factors are to be analyzed and tested using statistical methods. Normally-distributed data will be tested for differences between the intervention and control groups by using a two-sample *t*-test and non-normally-distributed data Wilcoxon rank-sum test. Categorical variables will be tested with a chi-squared test. Multivariable analysis will be conducted with potential confounders if the researcher and statistician find it relevant. Statistical software SPSS (IBM SPSS Statistics 21) will be used. The statistical significance will be set at p <0.05.

The activity diaries will be analyzed by counting the continuous length of sedentary periods and the amount of sedentary periods lasting longer than two hours. The activity periods and their lengths will be counted and summarized. These results will be assimilated into the data from the accelerometers and compared between the groups. Activity data will also be surveyed longitudinally over the whole 2.5-year treatment time and reported as descriptive summaries. Game diaries will be analyzed by counting the duration and frequency for the gaming and the games the participants have played the most. The qualitative data from the interviews will be analyzed with content analysis.

The results will be reported following the methodological guidelines for clinical trials outlined in the CONSORT statement [42].

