Some limitations of this study must be mentioned. Participation in the intervention study may cause the Hawthorne effect, leading to unusual behavior and biased results. We have not found a validation study for the Fitbit accelerometer and it has not yet been used widely for research purposes, which weakens the validity of the results. In addition, we recognize that including the accelerometer measure only twice during the study for each participant, according to the existing resources, weakens the study design. However, we have several other instruments to measure the primary outcome to reduce this possible limitation. Furthermore, the study runs over a long time period, which may have the effect of producing dropouts. In addition, the control group is also wearing the accelerometer and this may affect the behavior of the children, as they may become more motivated to be active.

This study also has several strengths. From a methodological point of view, the study protocol is built to provide diverse and reliable information from the phenomenon of interest. Randomization and blinding the physical therapists strengthens the study design. The follow-up throughout cancer treatment makes it possible to achieve valuable knowledge of the children’s activity in the long term.

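### Enrolling 40 keeps the required 34 children only if total loss stays at or below 15%, and the allowance for loss is justified by survival alone

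*Protocol article*

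**What the plan says.** In the Sample size calculation section the powered outcome is accelerometer activity. The effect is described as "targeting 360 gait cycles per day mean difference (assuming SD of 360 for the mean change) in the change between groups". From this the article concludes that "a total of 34 participants (17 to each group) would be needed to provide 80% power with a 5% significance level".

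The allowance follows in one sentence: "As the survival rate is over 80%, we increased the target enrollment by 20%, resulting in a sample size of 40 patients". No other reason for the increase is given, and no loss rate or number expected to be evaluable is stated.

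Four other places bear on this:
- Background gives the article's only survival figure, which is above 80% at 5 years after diagnosis.
- Outcome measurements and time-points of assessments has the accelerometer worn in the first week of the intervention and again at 1 year.
- Research ethics allows withdrawal at any time.
- The limitations part of the Discussion accepts that "the study runs over a long time period, which may have the effect of producing dropouts".

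**The concern.** Two things look wrong in the step from 34 to 40.

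First, an allowance for loss is made by dividing the required number by the proportion expected to remain. Multiplying by one plus the loss rate gives too few, and here the product was also rounded down. The enrolment therefore does not protect the required 34 at the loss level that the survival figure points to.

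Second, survival is a poor stand-in for having usable data. A child adds to the powered comparison only if accelerometer data exist. Death is one way to lose them. Withdrawal, illness in the measurement week and not wearing the device are others, and none is counted. The survival figure also belongs to a horizon of 5 years, not to the 1-year assessment.

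At stake is whether the stated 80% power is what 40 enrolled children deliver. The base calculation has little slack, since 17 per group gives only just over 80%.

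**Working it through.** **Inputs.** All are from the protocol article, mostly Sample size calculation: difference in change 360 gait cycles per day; SD of change 360; 17 per group; 80% power; 5% significance level; 20% increase; 40 enrolled. The two-sample t-test is from Data analysis. Sidedness is not stated. I assume two-sided because that reproduces the article's figure.

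**Step 1: reproduce 34.** Standardised effect = 360 / 360 = 1.0. A two-sided two-sample t-test (noncentral t) at 5% and 80% power needs 16.71 per group, so 17 per group and 34 in total. This matches exactly, and power at 17 per group is 80.7%. A one-sided test would need 13.1, so 14 per group, which does not match. The base figure is not in dispute.

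**Step 2: reproduce 40.** 34 × 1.2 = 40.8, stated as 40. The increase actually made is 40 / 34 = 1.176, or 17.6%.

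**Step 3: what a 20% loss would require.** 34 / (1 − 0.20) = 42.5, so 43. With equal groups, 17 / 0.8 = 21.25, so 22 per group and 44 in total.

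**Step 4: what 40 covers.** 34 / 40 = 0.85, so loss of up to 15%. At 20% loss, 40 × 0.8 = 32 remain, 2 short of 34.

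**Step 5: power by total loss from 40 enrolled** (t-test, effect 1.0 SD, loss equal in the two groups):

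| Total loss | Evaluable | Per group | Power | Enrolment needed to keep 17 per group |
|---|---|---|---|---|
| 15% | 34 | 17 | 80.7% | 40 |
| 20% | 32 | 16 | 78.1% | 44 |
| 25% | 30 | 15 | 75.3% | 46 |
| 30% | 28 | 14 | 72.1% | 50 |

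The 20% row is the ceiling implied by survival above 80%. The 25% and 30% rows are illustrative assumptions, because the article gives no dropout rate.

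**Step 6: basis of the allowance.** The reason given is survival, and the only survival figure is at 5 years. The powered measurement is made in week 1 and at 1 year. The article names other routes to loss (dropout and withdrawal) but attaches no number to them.

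**The case against.** The strongest reply is that the article never says 20% of children will be lost. Survival above 80% means deaths below 20%, so 20% is a ceiling. Because the figure is for 5 years, deaths by 1 year should be fewer. The 15% margin that 40 provides could then cover all deaths and leave room for some other loss. This stands. A reader might infer that the trial is underpowered, or that 32 is the number it will end with. The documents support neither, since they give no 1-year mortality and no dropout rate. They do not exclude a shortfall either.

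It can also be said that the gap is slight even at the ceiling: 2 children, and under 2 points below the 80% target. That is small beside the uncertainty in an assumed SD of 360. This stands too, and it limits the weight of the point.

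A reader might further infer that the rank-sum test named in Data analysis makes the shortfall worse. The plan uses that test only for data that are not normally distributed, and for such data its power may be lower or higher than that of the t-test. The documents do not allow a figure.

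The reply does not rescue the allowance itself. If 5-year survival overstates deaths by 1 year, it is the wrong basis, and the losses that the article does expect still have no stated share.

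**Conclusion.** The point holds in a limited form and is minor. The 20% increase was multiplied and rounded down, so 40 enrolled retains 34 evaluable children, and 80% power for a 1.0 SD difference, only while total loss is at most 15%. At 20% loss, power is 78.1%. Whether a shortfall arises depends on total loss, including withdrawal and missing accelerometer weeks, and the article gives no rate for these. The basis of the allowance is the more useful part to correct, because survival at 5 years describes neither the time point nor the ways in which the powered outcome can be missing.

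The power figures assume a two-sided t-test, the article's own difference and SD, and equal loss in the two groups.

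**What to change.** Keep 40 and restate what it provides. Suggested wording: *Forty enrolled children retain 80% power for a difference of 1.0 SD (two-sided t-test, 5% level) with up to 15% lacking accelerometer data. With 20% lacking data, power is about 78%. If, for illustration, 25% or 30% lacked data, equally in both groups, it would be about 75% or 72%.*

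Replace the survival argument with an allowance for missing accelerometer data from any cause (death, withdrawal, illness, device not worn) at the 1-year assessment.

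The cost is wording only: no added children, no change to design or analysis, and a slightly less favourable power statement.

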### Randomization and blinding

Participants are randomly assigned into the intervention and control groups. The randomization is conducted by a computer-generated list based on block randomization with randomly selected block sizes of 2 to 4. In the beginning, the participants do not know whether they are in a control or intervention group, although group contamination is possible as patients may be treated in the same unit making the blinding to the group allocation impossible. However, the information given before obtaining the informed consent is only exposing the aim of researching two different practices of advice and the outcome measurements. Blinding the researcher is not possible either because the researcher is personally giving the participants the intervention guidance. However, the researcher is not conducting the motor performance tests, so the risk for the researcher’s bias affecting the results is minor. The physical therapists that conduct the motor performance assessments are blinded to the group allocation and they do not know in which group the child is allocated unless the children reveal it by themselves.

### Adverse events

Serious adverse events due to the studied intervention are not expected. However, the adverse events may be difficult to recognize and distinguish from the treatment side effects. Active video gaming may cause light-adverse events such as muscle and joint ache and tiring eyes. Nintendo Wii™ health and safety precautions warn that “anyone who has had a seizure, loss of awareness, or other symptoms linked to an epileptic condition” should consult a physician before playing these games [29]. To ensure safety in this study, the treating oncologist checks the eligibility criteria and gives his/her approval for the patients to participate.

### Data analysis

The quantitative data from the activity and fatigue questionnaires, M-ABC scores, accelerometers and metabolic risk factors are to be analyzed and tested using statistical methods. Normally-distributed data will be tested for differences between the intervention and control groups by using a two-sample *t*-test and non-normally-distributed data Wilcoxon rank-sum test. Categorical variables will be tested with a chi-squared test. Multivariable analysis will be conducted with potential confounders if the researcher and statistician find it relevant. Statistical software SPSS (IBM SPSS Statistics 21) will be used. The statistical significance will be set at p <0.05.

The activity diaries will be analyzed by counting the continuous length of sedentary periods and the amount of sedentary periods lasting longer than two hours. The activity periods and their lengths will be counted and summarized. These results will be assimilated into the data from the accelerometers and compared between the groups. Activity data will also be surveyed longitudinally over the whole 2.5-year treatment time and reported as descriptive summaries. Game diaries will be analyzed by counting the duration and frequency for the gaming and the games the participants have played the most. The qualitative data from the interviews will be analyzed with content analysis.

The results will be reported following the methodological guidelines for clinical trials outlined in the CONSORT statement [42].

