**Methods:**

The aim of this study is to evaluate the effect of active video games in promotion of physical activity in children with cancer. The research is conducted as a parallel randomized clinical trial with follow-up. Patients between 3 and 16 years old, diagnosed with cancer and treated with vincristine in two specialized medical centers are asked to participate. Based on statistical estimates, the target enrollment is 40 patients. The intervention includes playing elective active video games and, in addition, education and consultations for the family. The control group will receive a general recommendation for physical activity for 30 minutes per day. The main outcomes are the amount of physical activity and sedentary behavior. Other outcomes include motor performance, fatigue and metabolic risk factors. The outcomes are examined with questionnaires, diaries, physical examinations and blood tests at baseline and at 2, 6, 12 and 30 months after the baseline. Additionally, the children’s perceptions of the most enjoyable activation methods are explored through an interview at 2 months.

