To assess *the metabolic risk factors*, each participant’s height, weight, body mass index, resting blood pressure, waist circumference, and fasting blood sugar and insulin concentrations are measured at all measurement points. Invasive tests are carried out within the normal blood tests of the cancer treatment procedures so that no additional needle punctures into the patients are required. Metabolic risk factors are examined, since childhood cancer survivors have been shown to be more insulin resistant and have higher cardiovascular risks than healthy children [59,60].

Eight weeks after the first measurement point, each child, and guardian if the child is under 10 years old, are interviewed by the researcher (LK). This interview includes open questions about physical activity, and each child is asked about their perceptions of the most enjoyed activation methods during their cancer treatment in the hospital and at home. The aim is to find out about children’s own ideas on how they would become more active and what they would like to have in the hospital to inspire them to physical activity. The children in the intervention group are also asked about their experiences of active video gaming to gain a deeper understanding about the intervention. The interviews are voice recorded if the child and his/her family are comfortable with it and provide their consent. There are multiple aims for this qualitative section of the trial [61]. First, we want to identify the needs of this target population regarding how they would like to be motivated and activated and how that activation could manifest during periods of treatment and isolation. Second, it is useful to know the reasons for why some participants dropped out or did not participate. Third, we want the participants to describe the problems, if any, in the intervention for further research and clinical purposes. In addition, the interviews will help to evaluate and clarify the overall study findings [61].

The baseline demographics of all the participants include the time of diagnoses, type of cancer, treatment received and information of the disease status. This information is collected from the electronic health records. The time points of assessment and the outcome variables are described in Figure 1.

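### The stated t-tests and Wilcoxon tests are valid but leave out the baseline value and age, and adjustment is left to later discretion; a pre-specified ANCOVA would gain modest to large precision

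*Protocol article*

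**What the plan says.** Data analysis names the tests for the activity and fatigue questionnaires, M-ABC scores, accelerometer and metabolic factors: "Normally-distributed data will be tested for differences between the intervention and control groups by using a two-sample" t-test, with the Wilcoxon rank-sum test for non-normal data. On covariates it says only: "Multivariable analysis will be conducted with potential confounders if the researcher and statistician find it relevant". The threshold is given as "The statistical significance will be set at p <0.05".

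Baselines are collected. The abstract schedules questionnaires, diaries, physical examinations and blood tests "at baseline and at 2, 6, 12 and 30 months after the baseline". The outcome section repeats this for the diary, and for the metabolic measures: "resting blood pressure, waist circumference, and fasting blood sugar and insulin concentrations are measured at all measurement points". The accelerometer is the exception. It is worn in the first week of the intervention and at 1 year, so no pre-intervention reading is described.

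The sample size section is framed in terms of change: "targeting 360 gait cycles per day mean difference (assuming SD of 360 for the mean change) in the change between groups". It concludes that "a total of 34 participants (17 to each group) would be needed to provide 80% power with a 5% significance level", and then "we increased the target enrollment by 20%, resulting in a sample size of 40 patients".

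**The concern.** Three features of the stated analysis are weak for this trial.

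- **Precision.** The sample is small and spans ages 3 to 16 with mixed diagnoses. No stratification is described under Randomization and blinding. A two-sample test leaves variance explained by age in the error term and does not make best use of the baseline value. BMI, waist circumference, blood pressure and activity are the outcomes most exposed, because no age-standardised score is stated for them.
- **Ambiguity.** The analysis section does not say whether the test is run on follow-up values or on changes. These are different analyses with different power.
- **Discretion.** Whether to adjust, and for what, is decided when the researcher and statistician see fit. The randomisation section says the researcher cannot be blinded. Covariates chosen after results are visible weaken a p-value close to 0.05.

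At stake are avoidable loss of power and an avoidable question about how the reported model was chosen.

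**Working it through.** **Inputs.** From Sample size calculation: difference 360, SD of change 360, 17 per group, 80% power, 5% level (two-sided assumed). From the outcome section: the leisure-time activity questionnaire correlates 0.26-0.40 with accelerometer data. Not in the document: the baseline-to-follow-up correlation ρ. It is assumed, and a range is shown.

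**Step 1: reproduce the plan's figure.** The standardised effect is 360/360 = 1.0. For a two-sample t-test with n per arm, the noncentrality is 1.0 × √(n/2) on 2n − 2 degrees of freedom. With n = 17 this is √8.5 = 2.92 on 32 df, and power is 80.7%. With n = 16 power is 78.1%. So 17 per group, 34 in total, reproduces exactly as an unadjusted t-test on a change score.

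**Step 2: variances.** Take equal variance σ² at baseline and follow-up.

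- Follow-up value: σ²
- Change: 2σ²(1 − ρ)
- ANCOVA: σ²(1 − ρ²)

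ANCOVA variance is therefore (1 + ρ)/2 of that of a change score, and 1 − ρ² of that of a follow-up value.

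**Step 3: power at 17 per arm.** The effect is 1.0 SD of the comparator's own measure, so each unadjusted test has 80.7%. The effective effect under ANCOVA is 1.0/√(variance ratio), on 31 df.

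| Assumed ρ | Ratio vs change | ANCOVA power | n/arm for 80% | Ratio vs follow-up | ANCOVA power | n/arm for 80% |
|---|---|---|---|---|---|---|
| 0.3 | 0.65 | 93.8% | 12 | 0.91 | 84.1% | 16 |
| 0.5 | 0.75 | 90.3% | 13 | 0.75 | 90.3% | 13 |
| 0.6 | 0.80 | 88.4% | 14 | 0.64 | 94.2% | 12 |
| 0.7 | 0.85 | 86.5% | 15 | 0.51 | 97.7% | 10 |
| 0.8 | 0.90 | 84.5% | 16 | 0.36 | 99.7% | 7 |

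The two comparators move in opposite directions as ρ rises, so it matters which one the plan intends. In summary I quote ρ from 0.8 to 0.3 against change and from 0.3 to 0.7 against follow-up. The last cell is left out of the summary so as not to claim the top end.

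**Step 4: age alone.** If age explained 10% of the variance (assumed), power at 17 per arm would go from 80.7% to 84.5%; at 30% it would be 92.1%.

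**Step 5: accelerometer.** With no pre-intervention reading, the step 3 gains are not available. The natural substitute is the baseline activity questionnaire. If its correlation of 0.26-0.40 carried over to follow-up accelerometer data, it would remove 0.26² = 0.07 to 0.40² = 0.16 of the variance.

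**Step 6: chance imbalance.** At 17 per arm the standard error of a baseline difference is √(2/17) = 0.34 SD. A difference of at least 0.3 SD in a given covariate has probability 2 × [1 − Φ(0.3/0.343)], about 38%. Moderate imbalance in age or baseline is therefore likely enough to plan for.

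**The case against.** A reader might infer that the plan ignores baseline altogether. The documents do not support that. The sample size is built on change and reproduces exactly as a t-test on change, which does use the baseline value. Against that comparator, the variance saving at ρ of 0.5, 0.6 and 0.7 is 25%, 20% and 15%. It is not the 25%, 36% and 49% that apply against follow-up values. This stands and limits the size of the point. What remains is that the analysis section never says which of the two is meant, and that ANCOVA has the smaller variance against either at every correlation shown.

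The 1.0 SD effect is also the design effect for the accelerometer, which is the one measure without a baseline to adjust for. That stands too: the power figures serve as a yardstick for the other outcomes and are not a forecast for the main device.

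Age is partly handled already, since M-ABC2 and the PedsQL fatigue scale have age-related scores. The age argument therefore applies mainly to activity, BMI, waist and blood pressure; for M-ABC2 and fatigue the gain comes from the baseline value.

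Nor is adjustment wholly absent. The Participants section says treatment duration and dose will be taken into account, and the Intervention section says the same of physical therapy records. But the named two-sample tests cannot do this, and no model is tied to those promises.

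Finally, an article may leave covariate lists and model details to an analysis plan. That is accepted. The point rests on what the article does fix: the test, and a rule that adjustment is discretionary.

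**Conclusion.** The point holds as one of efficiency and pre-specification. The stated tests are valid under randomisation; to call them invalid or biased would go too far. They give up precision that the collected data could supply, and the adjustment rule leaves a choice open to an unblinded researcher.

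At 17 per arm and an effect of 1.0 SD, baseline-adjusted ANCOVA would raise power from 81% to about 84-94% against a t-test on change, or to about 84-98% against a t-test on follow-up values. These figures rest on assumed correlations (0.8 to 0.3 and 0.3 to 0.7 respectively), equal variances over time and a two-sided 5% test. Because the document gives no correlation, a claim that most of the precision is lost is not supported; modest to large is the fair description. For the accelerometer only a small gain should be expected. The change is worth making, but the trial does not fail without it.

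**What to change.** Before any unblinded look at outcome data:

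1. For each outcome with a pre-intervention value (questionnaires, diary, M-ABC2, fatigue, metabolic factors), make the main analysis an ANCOVA on the follow-up value with group, baseline value and age. Centre is optional.
2. Keep the t-test or Wilcoxon test as a sensitivity analysis, and say whether it is run on follow-up values or changes.
3. Analyse BMI as an age- and sex-standardised score, or adjust it for age.
4. For the accelerometer, do not treat the week-1 reading as a baseline. It is taken under intervention, so change from it, or adjustment for it, could remove part of the effect. Adjust for age and the baseline activity questionnaire instead, and reconcile the change-based sample size with the absence of a pre-intervention reading.
5. Replace the discretionary sentence on multivariable analysis with the named covariates.

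The cost is analysis-plan wording and a few degrees of freedom. No new data are needed, and the planned software (SPSS) fits these models.
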